## 3. Results

Thin-slice 3D MRI examination with reconstruction can answer all relevant questions for preoperative planning instead of CT. EOS or X-ray examination in combination with MRI data is sufficient for imaging pedicles and spinal deformity.

We expect to be able to replace preoperative CT diagnostics and obtain further information by incorporating an additional 3D MRI sequence. We anticipate that through this method, using MRI in combination with X-ray or EOS data, we will be able to detect and assess both preoperative and diagnostic parameters in a single examination. This includes parameters such as pedicle thickness according to Wanatabe, degree of disc degeneration, intraspinal anomalies, as well as formation and segmentation disorders of the vertebral bodies. Our goal is to completely eliminate the need for preoperative CT examinations by relying solely on MRI.

2.The Cobb angle in the radiograph correlates with the calculations from the back scanner image, and follow-up checks can be replaced by a three-dimensional back measurement (radiation-free).

The parameters obtained from the back scanner regarding the sagittal profile of the spine have already been validated in the general population [19]. In the context of our study, we expect a correlation between the data from the back scanner and the data from EOS and X-ray imaging, enabling the evaluation of the coronal plane and the Cobb angle in patients with severe scoliosis.

3.Correlations between dental anomalies (e.g., crossbite) and scoliosis can be proven [31,32,33,34].

We expect to find existing correlations between upper body posture and bite position, particularly in patients with severe scoliosis.

## 4. Discussion

So far, there is no standard for the preoperative diagnosis of juvenile patients with scoliosis. If scoliosis is suspected, X-ray images of the spine are obtained [40,47,48,49,50]. These allow the scoliosis form to be classified and the Cobb angle to be determined [51]. Depending on the extent of the scoliosis, a surgical indication is made. Currently, it is up to the surgeon to decide what type of imaging is needed preoperatively. It is the surgeon’s individual decision whether functional images, computed tomography, or magnetic resonance imaging are required for surgical planning and to exclude underlying or concomitant malformations or space-occupying lesion [40,49,52]. The assessment of the bone with the question of screw-bearing pedicle thickness, hemivertebra to be resected, or partial vertebral body fusion has so far been performed by computed tomography but could possibly also be clarified by MRI with appropriate follow-up. Less severely affected patients with milder degrees of scoliosis may also benefit from alternative imaging modalities and preoperative MRI as intraoperative risks can be reduced. Although they rarely require a CT scan initially and can often be treated with conservative therapies, their response to therapy needs to be closely monitored with follow-up examinations, which have previously included radiographic imaging. According to the Federal Office for Radiation Protection, this would save approximately 770 µGym^2^ per X-ray examination, which can be dispensed with by using a back scan, among other things.

If surgical therapy is planned, concomitant anomalies should be excluded before spinal stabilization. In particular, dysraphic anomalies (e.g., cleft medullary malformations, spinal lipoma, fatty filum terminale, secondary tethered cord syndrome), which are highly likely to cause clinically relevant tethered cord syndrome, can be detected with preoperative MRI examination, which has not been performed as the standard so far, and subsequently taken into account for surgical planning. Developmental anomalies in the craniocervical junction (e.g., Chiari type I and II malformations, basilaris intussusception) can cause severe neurological deficits, especially in the absence of preoperative knowledge during surgical scoliosis treatment, if not taken into account during intubation or head positioning, and can be easily detected with our standard MRI examination. Patients with nerve sheath tumors or other causes of significant spinal stenosis in a pediatric patient cohort must also be diagnosed prior to any spinal intervention. Adequate MRI imaging is a prerequisite for significantly reduced intraoperative risk in young patients already characterized by a spinal deformity. Close interdisciplinary cooperation between neuroradiology, orthopedics, and pediatric neurosurgery is key to the success of this project and the smooth and safe treatment of our young patients with a mid- to long-term aim of establishing this kind of set up as the gold standard for treatment and diagnostics for juvenile patients with scoliosis. The initial step is always to take a detailed medical history, including family history, and, in female patients, to determine the time of menarche, if possible. With the onset of menarche, residual skeletal growth can be expected for a further two to two and a half years. In boys, an equivalent process takes place about two years after the onset of voice change [53,54]. The clinical examination follows the anamnesis. This includes, among others, a survey of the mobility of the spine in the form of the forward bending test according to Adams with the use of a scoliometer [49,55]. The scoliometer has a high interobserver reliability [40,47,48,49,50]. Whereas Coelho et al. [50] found a meaningful association with the radiologically determined Cobb angle, other authors described an investigator or BMI dependence [55]. In summary, the aim of the present project is to replace the above-mentioned scoliosis analysis parameters with alternative examination procedures without X-rays. Taking into account the increased sensitivity of children to radiation and its potential long-term consequences, alternative procedures without the use of ionizing radiation are particularly desirable [56]. In particular, CT examinations in childhood have been shown to increase the risk of leukemia and triple the risk of developing a brain tumor. Particularly in cases of disease requiring intermediate or follow-up examinations, the procedure of video-raster stereography and the associated visualization of spinal topography offers a potential, noninvasive alternative, because video-raster stereography has been shown to be a valuable tool to determine back geometry [19]. If the back scanner is suitable as an intermediate diagnostic procedure in the future, it could also support medical diagnostics in countries where financial resources play an even greater role. According to Ohlendorf et al. [46], studies have been published regarding the normal values of upper body posture as a function of age decade (starting at 20 years) and sex using this same measurement system [19]. In summary, men and women have a balanced, upright, and symmetrical upper body posture regardless of age. Those standard values can help in decision making for therapeutic or clinic interventions as well as in the evaluation of therapeutic interventions. Therefore, they could also be used as reference values for the present project, and, if necessary, back scanners could be used for screening examinations in adolescents. Of course, bite location data are not used in providing less radiation or safer scoliosis surgery. However, analyses of the correlation between temporomandibular malpositions and upper body posture would also help (dental) practitioners diagnose anomalies of the temporomandibular system (e.g., crossbite, temporomandibular joint disorders) and in the dorsal upper body posture (e.g., scoliotic malposition, kyphotic developments in the thoracic spine) at an early stage in order to prevent progression.

### Limitations

For both the three-dimensional back scanner and the introaral scanner, studies have mainly focused on adults [19]. Age-related values of the upper body posture for children and adolescents are not currently available and will be collected in another project. Results are expected before this study is completed. One problem is the age of the subjects during the MRI. The younger the patient, the lower the fat content in the bone and, consequently, the more reduced the signaling. Consequently, the differentiation of ligaments, membranes, and bones could be more difficult. Also, the duration of the examination could be problematic, especially in younger patients, as they have to lie still for about 30 min in the MRI. This can lead to motion artifacts and measurements having to be repeated or not being able to be evaluated.

We acknowledge that this study protocol primarily focuses on detailing the methodology of our project. While initial results would undoubtedly add valuable context, the complexity and multifaceted nature of our study necessitate a dedicated and thorough description of the methods. Combining this with the results in a single manuscript could obscure the holistic and interdisciplinary approach that is central to our research. To address this, we present this study protocol to offer a comprehensive overview of our prospective clinical research project. By doing so, we aim to enhance transparency in prospective clinical research and reduce publication bias by ensuring the reproducibility of our study design and analysis.

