### 2.2. Participants/Study Subjects/Sample Size Calculation

The sample size calculation will be based on our primary hypothesis. To evaluate whether thin-slice MRI examination with reconstruction can adequately address the relevant questions for preoperative planning instead of CT, we will determine the Wanatabe classification for pedicle type based on both MRI and CT data and calculate Cohen’s kappa. Our goal is to demonstrate a Cohen’s kappa of more than 0.4 (indicating at least moderate agreement according to standard classification) using a one-sided test with a significance level of alpha = 5%. For sample size planning, we will simplify our assumptions by considering that the categories are approximately equally populated and that there is, in fact, at least substantial agreement with a kappa of 0.75. In this scenario, at least 30 patients will be sufficient to achieve a statistical power of 95%, even with a 5% drop-out rate. A relatively high power was chosen to account for an uneven distribution and to ensure sufficient statistical power overall. For the correlation tests involving quantitative measures of the secondary objectives, we also expect adequate statistical power. In general, statistical tests will be conducted with a two-sided approach and a significance level of alpha = 5%, except for the primary objective.

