Within the framework of the project, at least 50 male and female children and adolescents aged > 7 to 18 years will be analyzed (according to the calculated power analysis). All of them will present to the Orthopaedic Clinic of the University Hospital Frankfurt with a clinical picture of scoliosis between 2022 and 2025. Height and weight will be recorded at admission. In addition, a separate medical history form will be used to record any previous conservative therapies (orthotics, braces, physiotherapy), including the type and duration of treatment. The following criteria apply for inclusion in this study:-Children/adolescents diagnosed with severe scoliosis by major curve in the X-ray > 40° [36];-Planned MRI examination of the spine at the Institute of Neuroradiology;-An EOS and/or a CT examination of the spine has already been performed as part of the diagnosis or must still be planned independent of the present project;-Children must be able to cooperate (>7 years, no motor or cognitive impairment);-Consent of the legal guardians as well as of the child.-The following criteria apply for exclusion from this study:-There will be no upper curve limit as an exclusion criterion;-Previous spinal surgery;-Mental and/or physical impairments that do not warrant a 30 min MRI scan or contraindications to an MRI scan (i.e., implants, pregnancy).

Informed consent from a parent and/or legal guardian for study participation will be obtained.

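### The primary MRI–CT kappa is pooled over ages >7 to 18 although the protocol expects weaker MRI bone signal in younger patients; agreement by age should be reported and the replace-CT conclusion worded to match

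*Protocol article*

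**What the plan says.** - **Limitations.** The protocol names patient age as a problem for MRI: "The younger the patient, the lower the fat content in the bone and, consequently, the more reduced the signaling". The stated consequence is that "the differentiation of ligaments, membranes, and bones could be more difficult". The effect is not quantified.
- **Section 2.2, sample size.** The primary comparison is pedicle type on MRI against CT. "Our goal is to demonstrate a Cohen’s kappa of more than 0.4", tested one-sided at 5%. Planning assumes that "the categories are approximately equally populated" and that "there is, in fact, at least substantial agreement with a kappa of 0.75". One kappa serves for all patients. Thirty patients are said to give 95% power with 5% drop-out.
- **Section 2.2, participants.** At least 50 "children and adolescents aged > 7 to 18 years will be analyzed". There are no age strata and no minimum number of younger children.
- **Section 2.3, statistical data analysis.** The single-kappa test against 0.4 is repeated. Age is listed among the demographic variables for descriptive statistics and exploratory comparisons.
- **Section 3.** "Our goal is to completely eliminate the need for preoperative CT examinations by relying solely on MRI". No age restriction is attached.
- **Table 1.** Pedicle type has four categories, A to D.

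**The concern.** The protocol gives a reason why the MRI reading of a bony endpoint may be less accurate in younger patients. Neither the primary criterion nor the wording of the conclusion takes this up. The issue is scans that can be read but are read less accurately, which is separate from scans lost to motion.

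A pooled kappa mainly reflects whichever ages supply most of the pairs. If most are adolescents, good agreement there can carry the test while agreement among the younger children is low. The result would then be stated for the full age range. Sections 1 and 4 tie pedicle assessment to screw placement, and section 4 stresses children's sensitivity to radiation. A reader will therefore want to know at which ages MRI has been shown to agree with CT.

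**Working it through.** **1. The protocol's own figure.** Inputs from section 2.2 and Table 1: null kappa 0.4, true kappa 0.75, one-sided 5%, power 95%, equal categories, four types.

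With equal margins over four categories, chance agreement is pe = 0.25, observed agreement is po = pe + κ(1 − pe), and the large-sample SD of kappa per patient is s = √[po(1 − po)] / (1 − pe).

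- κ = 0.40: po = 0.55, s0 = √0.2475 / 0.75 = 0.663
- κ = 0.75: po = 0.8125, s1 = √0.1523 / 0.75 = 0.520
- Null and alternative variances: n = [1.645 × (0.663 + 0.520) / 0.35]² ≈ 31 evaluable; 31/0.95 gives 33 recruited
- Alternative variance only: n = [1.645 × 2 × 0.520 / 0.35]² ≈ 24 evaluable; 24/0.95 gives 26 recruited

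The stated 30 lies between these variants. The sample size is not in dispute.

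**2. What pooling does to kappa.** With equal margins and a fraction f of younger patients, pooled κ ≈ (1 − f)κ_old + f·κ_young. The values of f and κ_young are assumptions, because the protocol gives neither. κ_old is set at the planning value of 0.75.

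- κ_young = 0.2, f = 10/20/30%: pooled κ ≈ 0.695 / 0.64 / 0.585
- κ_young = 0, f = 10/20/30%: pooled κ ≈ 0.675 / 0.60 / 0.525
- With κ_young = 0, pooled κ falls to 0.4 only when 0.75(1 − f) = 0.4, so f = 0.35/0.75 = 46.7%

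**3. Chance that the pooled test succeeds.** This was simulated with one pair per patient, four equal categories, and success defined as a one-sided 95% lower limit (large-sample standard error) above 0.4. With no younger patients, success is about 95% at N=30 and 99% at N=50.

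| κ in younger | Share younger | N=30 | N=50 |
|---|---|---|---|
| 0.2 | 10% | 86% | 96% |
| 0.2 | 20% | 71% | 86% |
| 0.2 | 30% | 50% | 66% |
| 0 | 10% | 82% | 94% |
| 0 | 20% | 57% | 73% |
| 0 | 30% | 27% | 36% |
| 0 | 40% | 8% | 9% |

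**4. What age-specific data could show.** If the true kappa in the younger group is 0.75, the one-sided 95% lower limit is about 0.75 − 1.645 × 0.520/√n. That gives 0.37 at n=5, 0.48 at n=10 and 0.53 at n=15, which is rough at such small n. A powered test in each of two age strata would need 24–31 evaluable patients per stratum. With drop-out that is 2 × 26 to 2 × 33, or 52–66 in all, against 30 calculated and at least 50 planned.

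**The case against.** - **Subgroup tables belong in the SAP.** An age analysis may exist there, and nothing in the article excludes one. This stands: a missing subgroup table alone would be no finding. What remains is in the article itself. It names an age-dependent weakness of MRI and then words the replacement of CT for everyone.
- **The Limitations text is cautious.** It says differentiation could be harder. A reader might infer that MRI cannot type the pedicle in the youngest children, or that the trial is set to declare CT dispensable at ages where MRI fails. The documents support neither. No loss of accuracy is quantified, kappa 0 is a worst case, and section 3 states goals and expectations and not a rule triggered by the kappa test.
- **The scenarios are assumed.** This also stands. Section 2.2 sets 0.75 for the whole sample, and the illustration assigns it to older patients only. A younger-group kappa of 0.5 or 0.6 would exceed the trial's own limit and mislead nobody. When the affected group is large and agreement is nil, the pooled test usually fails. One pair per patient and CT in every patient are also simplifications: section 2.1 says CT exists only in some cases.
- **Small age bands should not gate the conclusion.** Correct. Five younger patients with a true kappa of 0.75 would have a lower limit of about 0.37, below 0.4. Band-specific kappa also moves with the mix of pedicle types. The remedy should therefore estimate agreement and not test it band by band.

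**Conclusion.** The point holds as a cheap improvement. The pooled test is a legitimate primary analysis and its sample size can be reproduced. It cannot show whether agreement holds at the ages where the protocol itself expects MRI to be weaker, and the wording in section 3 does not carry that caveat. Under the assumptions in the table, with 10–30% younger children at kappa 0.2, the test would still succeed in about 86–50% of trials with 30 pairs and 96–66% with 50. At kappa 0 the ranges are about 82–27% and 94–36%. The direction of the effect comes from the protocol. Its size rests on a share and a kappa that the protocol does not give.

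**What to change.** 1. Leave the pooled kappa test as the primary analysis and the sample size unchanged.
2. Prespecify a supporting analysis of MRI–CT raw agreement and kappa by age, with 95% intervals and the number of pairs at each age. Either model agreement on continuous age or use bands fixed before the data are seen. Raw agreement should stand beside kappa because kappa depends on the mix of pedicle types.
3. State in sections 2.3 and 3 that the replace-CT conclusion is worded for the ages actually represented. It is to be reported as unconfirmed for younger children if their estimate is low or too imprecise. There should be no separate pass/fail test per band.

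The cost is one table from data already collected and one qualifying sentence. The downside is a wide interval for the youngest patients and possibly a narrower claim.

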### 1.2. Study Questions

(1)Can MRI examination with additional thin-slice 3D reconstruction answer all relevant questions for preoperative planning instead of CT? Are EOS or whole spine X-ray examinations in combination with MRI data sufficient for the evaluation of the pedicles and spinal deformity?(2)Does the Cobb angle in the radiograph correlate with the calculations from the back scanner image and can follow-up checks be replaced by this video-raster stereography measurement (radiation-free)?(3)Are there any correlations between dental anomalies (e.g., crossbite) and scoliosis?

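### The primary MRI–CT kappa on pedicle types A–D has no place for the non-evaluable MRI scans that the article foresees, so it describes agreement only where MRI was readable

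*Protocol article*

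**What the plan says.** Section 1.2 (Study Questions) puts the first question in replacement terms: "Can MRI examination with additional thin-slice 3D reconstruction answer all relevant questions for preoperative planning instead of CT". Section 3 (Results) carries this to the expected conclusion that preoperative CT will no longer be needed at all.

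One formal test is fixed for this question. Section 2.2 and the statistical data analysis part of Section 2.3 both set it as a one-sided 5% test that Cohen's kappa between MRI and CT exceeds 0.4. Section 2.2 bases it on the Watanabe pedicle type, and Table 1 gives the range of that variable as A, B, C, D. The planning assumption is that "the categories are approximately equally populated and that there is, in fact, at least substantial agreement with a kappa of 0.75". Section 2.2 concludes that "at least 30 patients will be sufficient to achieve a statistical power of 95%, even with a 5% drop-out rate". It does not say what counts as drop-out. The same section later states that "at least 50 male and female children and adolescents aged > 7 to 18 years will be analyzed".

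The Limitations section expects a weaker bone signal the younger the patient, which could make bone harder to tell from ligament and membrane. It adds that the scan duration could be a problem, especially in younger patients: "This can lead to motion artifacts and measurements having to be repeated or not being able to be evaluated".

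**The concern.** A kappa needs a category from both methods. A pedicle that CT can classify and MRI cannot has no cell in an A–D by A–D table. The analysis as written can therefore use only the pairs in which MRI gave an answer. For a question about replacement, a readable CT beside an unreadable MRI is the plainest instance of MRI not doing the job, and this statistic cannot register it.

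The article itself suggests that any such losses would fall more on younger patients. Its Discussion gives children's sensitivity to radiation as a reason for the project. A kappa from readable scans only could thus be quoted for a wider group than the one that produced it.

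**Working it through.** **Inputs from the article (Section 2.2, Table 1).** Null kappa 0.4; assumed kappa 0.75; one-sided alpha 5%; power 95%; drop-out 5%; four categories, taken as equally filled; one rating per patient; 30 patients required, at least 50 planned.

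**Assumption, not in the article.** A share *u* of MRI readings is non-evaluable, unrelated to CT category, with *u* between 5% and 20%.

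**Step 1: the plan's own figure.** I used the Fleiss–Cohen–Everitt large-sample variance for four equal categories. The unit variance is v0 = 0.440 at kappa 0.4 and v1 = 0.271 at kappa 0.75.

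- Null and alternative variances: n = [1.645 × (√0.440 + √0.271) / 0.35]² = 30.9, so 31 evaluable pairs. 31/0.95 = 32.6, so 33 patients.
- Alternative variance only: n = [(1.645 + 1.645) × √0.271 / 0.35]² = 23.9, so 24 pairs. 24/0.95 = 25.3, so 26 patients.

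The stated 30 lies between these. With 30 × 0.95 = 28.5 pairs, power is 93% by the first formula and 97% by the second. The sample size statement is reproduced and is not at issue.

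**Step 2: kappa when non-evaluable MRI counts as non-agreement.** CT margins are 0.25 each. MRI margins are (1 − u)/4 each, plus u in a fifth outcome that CT never takes. With k the kappa among evaluable scans:

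- observed agreement po = (1 − u)(0.25 + 0.75k)
- chance agreement pe = (1 − u)/4
- kappa = (po − pe)/(1 − pe)

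For k = 0.75 the bracket in po is 0.8125. At u = 10%: po = 0.90 × 0.8125 = 0.731, pe = 0.225, kappa = 0.506/0.775 = 0.653.

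**Step 3: power.** Power = Φ{[kappa − 0.4 − 1.645√(v0/N)] / √(v/N)}. Here v is the unit variance of the table with the fifth outcome: 0.293, 0.307, 0.314 and 0.314 at u = 5%, 10%, 15% and 20%. If failures are left out instead, kappa stays 0.75, N is the number of remaining pairs and v = v1. Simulated power of the Wald test is in brackets.

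| u | kappa, failures counted | Power at 30, counted | Power at 30, left out (pairs) | Power at 50, counted |
|---|---|---|---|---|
| 5% | 0.701 | 85% (87%) | 93% (28) | 97% (97%) |
| 10% | 0.653 | 70% (76%) | 92% (27) | 90% (92%) |
| 15% | 0.607 | 53% (62%) | 91% (26) | 75% (81%) |
| 20% | 0.5625 | 36% (47%) | 88% (24) | 54% (64%) |

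The simulated test rejects slightly too often at kappa 0.4 (6.2% at n = 30), so the bracketed figures are a little generous. The last column supposes that all 50 have a CT; Section 2.1 says CT is available only in some cases.

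**Step 4: where the point value reaches 0.4.** Write w = 1 − u. For k = 0.75, 0.5625w/(1 − w/4) = 0.4 gives 0.6625w = 0.4, so w = 0.604 and u is about 40%. If agreement among evaluable scans were only 0.50 (again an assumption), kappa would be 0.319/0.7875 = 0.405 at u = 15% and 0.30/0.80 = 0.375 at u = 20%.

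**The case against.** A reader might infer that the plan discards failed scans under its 5% drop-out allowance. The document does not say so. Section 2.2 leaves drop-out undefined, and the Limitations section mentions neither drop-out nor exclusion. The A–D entry in Table 1 lists the values of a classification; it is not a rule on the analysis set. A handling rule may also stand in a fuller protocol or analysis plan that is not shown.

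A reader might also infer that failures will be common or would overturn the result. That is not supported either. The wording describes a possibility and names repetition first, which may recover some scans. Section 2.2 requires children who can cooperate and excludes impairments incompatible with a 30-minute scan, so the rate may be low. Under the plan's own kappa of 0.75 the point value stays above 0.4 until about 40% are non-evaluable. Falling below 0.4 within 5% to 20% needs a second assumption, such as agreement of 0.50, that the article does not make.

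Lastly, coding failures as disagreement is one convention; reporting their proportion beside the kappa is another legitimate one. Making success depend on both kappas would cost power: N for 95% power rises to 44, 63 or 154 at 5%, 10% or 20% non-evaluable.

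All of this stands. It does not remove the mismatch: the measure and its scale are fixed in the article, and they cannot show how often MRI gave no answer, which is part of the question that the article asks.

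**Conclusion.** The point holds in limited form. As described, the primary kappa measures MRI–CT agreement among scans that MRI could classify, and the conclusion planned from it is wider than that. Nothing in the article shows that failed scans are treated as drop-outs, and the stated 30 patients are not wrong.

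The size depends on a failure rate that the article does not give. At an assumed 5%, kappa moves from 0.75 to 0.70 and the conclusion would rarely change. At an assumed 20% it moves to 0.56, and power at 30 patients is about 36% (47% simulated) against 88% if the failures are left out. At such rates the handling rule could decide whether the test succeeds. These figures assume equal categories, one rating per patient, and failures unrelated to CT category and to agreement among the rest. If the hard-to-read scans would also have been the discordant ones, a kappa on readable scans would flatter MRI further; the article gives no figure for this.

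**What to change.** 1. Record non-evaluable as a possible MRI outcome for the pedicle classification, after any repeat measurement. Keep drop-out for withdrawal or an examination that was not done.
2. Report the proportion of non-evaluable MRI, overall and by age, beside the primary kappa.
3. Add one pre-stated sensitivity kappa in which a non-evaluable MRI with an evaluable CT counts as non-agreement.
4. State that the replacement conclusion will be limited to evaluable scans if the two analyses differ materially, and say beforehand what difference counts as material.

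If a rule already exists in a document that is not shown, stating it in the article settles the handling question; the proportion should still be reported.

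The primary test, its 0.4 bar and the sample size can stay as they are, and no second formal success criterion is needed. The cost is one extra code on the score sheet, one extra analysis and possibly a less favourable figure to report. Patient management does not change.
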